##### Additional analysis in the UK Emulated Trial making use of data on treatment prescription dates

A limitation of this approach is that it assumes individuals with A=1 at time 1 have been taking azithromycin for the past 12 months. Realistically, individuals may initiate treatment with azithromycin at any time between time 0 and time 1. For the most recent time period, we can conduct a second analysis using the UK data and making use of data on treatment prescription dates.

In this second analysis, AIPTW is used as above, but the outcome model used previously (equation 3) is modified to include a variable indicating time and an interaction term between time and treatment. We define a new time variable, $t^{*}$, which measures time in months. For treated individuals, $t^{*}=0$ on the first date they are prescribed azithromycin after the index visit. For control individuals, $t^{*}=0$ for the date of the index visit. We let $Y_{t^{*}=12}$ denote FEV_1_% measured on the day of the annual review after $t^{*}=0$ and closest in time to $t^{*}=12.$ Note that this accommodates the fact that annual review visits do not always take place exactly 12 months apart. The outcome model will then be defined as:

(6)
$$Y_{t^{*}=12}=\delta_{0}+\delta_{A}A+\gamma_{c}C+\delta_{t^{*}}t^{*}+\delta_{At^{*}}At^{*}+\epsilon$$

After fitting this model, we set $t^{*}=12$ to obtain the relevant expected outcomes.

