##### UK CF Registry Data

Using annual review data only

Within the period p, the index visit for a given individual is the first annual review visit at which they meet the eligibility criteria in the 2-year recruitment period. The follow-up visit is the date of the next annual review which is closest to 12 months after time 0, but falls within 9–15 months after time 0. The outcome is FEV_1_% measured on the day of the follow-up visit. Individuals are included in the treated group if they are recorded as being prescribed azithromycin at the follow-up visit because the information recorded on treatment use at the annual review refers to treatment use over the past year. Individuals not recorded as being prescribed azithromycin at the follow-up visit are included in the control group.

Using annual review data and prescription dates data

In the UK Registry, prescription dates data are available from 2016 onwards. Therefore, in period 3 (2016–2018), we can conduct a second analysis making use of the dates data for a more precise time 0. In the second analysis, the index and follow-up visits are defined as above for individuals in the control group. For treated individuals, the index visit is defined similarly; however, time 0 is defined as the first date post-index visit at which azithromycin is prescribed. The follow-up visit is defined as the next annual review visit which is closest to 12 months after time 0, but falls within 9–15 months after time 0.

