#### Main analysis

In the target trial, the authors investigated the change in FEV_1_% from baseline, with adjustment for baseline FEV_1_%. This is equivalent to a regression of the mean FEV_1_% at follow-up with adjustment for baseline FEV_1_%. We note that in the absence of imbalance between treatment groups in baseline FEV_1_%, the adjustment of baseline FEV_1_% is not required but may result in gains in efficiency. Both approaches result in estimates of the ATE as defined in equations(1)  (2).

In the emulated trials, we need to account for differences between treatment groups at baseline, including baseline FEV_1_%. We also require assumptions of positivity, no interference, consistency and conditional exchangeability (conditional on C). We use augmented inverse-probability-of-treatment weighting (AIPTW) to control for potential confounding by C. AIPTW involves defining models for the treatment and outcome. This approach was chosen as it is doubly robust, meaning that it gives consistent estimates of treatment effects if either the treatment model or outcome model is correctly specified.^27^ This represents an advantage compared with the alternative propensity score or outcome-regression based approaches which are singly robust.

The first step in implementing AIPTW is to estimate the propensity scores, that is, the probability of treatment conditional on baseline covariates:

(3)
PS=P(A=1|C)

Propensity scores will be estimated using logistic regression, including C as linear terms.

In the second step, we specify an outcome model conditional on treatment and covariates:

(4)
$$Y_{1}=\gamma_{0}+\gamma_{A}A+\gamma_{C}C+\varepsilon$$

The AIPTW estimator for

(5)
$$\hat{E}[Y_{1}(a)]=\frac{1}{n}\sum_{i=1}^{n}\left\{\frac{I(A_{i}=a)Y_{1i}}{\hat{P}(A_{i}=a|C_{i})}-\frac{I(A_{i}=a_{i})-\hat{P}(A_{i}=a|C_{i})}{\hat{P}(A_{i}=a|C_{i})}\hat{E}(Y_{1i}|A_{i}=a,C_{i})\right\}$$

where $\hat{P}(A_{i}=a_{i}|C_{i})$ can be obtained using predictions from the propensity score model. The estimator in equation 5 can be used to estimate $E\left[Y_{1}\left(0\right)\right]$ and $E[Y_{1}(1)],$ and the difference between these two expectations is an estimate of the average treatment effect in the population. Standard errors can be obtained based on the efficient influence function.^28^

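### UK prescription-date analysis: predicting at month 12 inside the AIPTW formula, while outcomes stay at their actual review dates, removes the intended visit-timing correction

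*Protocol article*

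**What the plan says.** The section on the additional UK analysis with prescription dates carries the estimator over from the main analysis ("In this second analysis, AIPTW is used as above") and alters only the outcome model, which "is modified to include a variable indicating time and an interaction term between time and treatment" (equation 6). The carried-over estimator is equation 5 in the Main analysis section, which has a single place for a predicted outcome given arm and covariates.

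The outcome is FEV1% "measured on the day of the annual review after" the time origin and closest to month 12. The protocol acknowledges that "annual review visits do not always take place exactly 12 months apart". The closing instruction is: "After fitting this model, we set $t^{*}=12$ to obtain the relevant expected outcomes".

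The clock differs by arm. Under UK CF Registry Data: "For treated individuals, the index visit is defined similarly; however, time 0 is defined as the first date post-index visit at which azithromycin is prescribed". For controls it starts at the index visit. The outcome review must fall 9 to 15 months after time 0. The propensity model contains only the covariates C, so `t*` does not enter the weights. The estimand, under Causal estimand of interest, is the difference in mean FEV1% at month 12.

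**The concern.** Equation 6 is there to bring outcomes measured at unequal times to a common month 12. Equation 5 uses one prediction both as the leading term and inside the residual. If that prediction is made at month 12 while the outcome stays at its actual date, the residual is not centred at zero even when equation 6 is correct. It contains the timing offset that the leading term has just removed.

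Readers would believe that visit timing had been adjusted for, while a difference between arms in mean time since time 0 would pass into the treatment effect. The protocol's Limitations section relies on this analysis to address, in part, uncertain start dates and uneven review intervals. The main analysis also chose AIPTW for its double robustness, and that property would no longer hold for the month-12 estimand.

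**Working it through.** The protocol gives no figure to reproduce, so the check is algebra on equation 5, then simulation, then a size estimate under stated assumptions.

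**1. Rewrite equation 5.** Its second term prints I(A_i=a_i), read here as the standard I(A_i=a). With m for the predicted outcome and P for P(A=a|C):

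`mean{ I·Y/P − (I − P)/P·m } = mean{ m + (I/P)·(Y − m) }`

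**2. Insert the instruction.** Put m = m(a,C,12) in both places. The outcome is at the actual date, so under equation 6 `Y = m(a,C,t*) + error`. If P is right, the weighted residual averages

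`slope_a × (weighted mean t*_a − 12)`, with slope_0 = δ_t and slope_1 = δ_t + δ_At.

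This cancels the move to month 12. Equivalently, the difference from AIPTW without a time term is `mean{ (1 − I/P)·[m(a,C,12) − m_no-time(a,C)] }`, which has expectation zero when P is right.

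**3. Bias for the month-12 contrast.**

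`slope_1 × (mean t*_1 − 12) − slope_0 × (mean t*_0 − 12)`

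**4. Simulation.** Assumptions not in the documents: n = 2,000, 400 replicates, true month-12 effect 2.00, residual SD 8, visit-time SD 0.8 months, visits kept within 9–15 months. The estimator SD is about 0.45, so the Monte Carlo error of a mean is about 0.45/√400 = 0.02.

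| Scenario | As written | No time term | Observed `t*` in residual |
|---|---|---|---|
| Treated 1 month later, slopes −0.17 in both arms | 1.845 | 1.846 | 2.052 |
| Treated 1 month later, slopes −0.5 control, −0.2 treated | 1.813 | 1.812 | 2.002 |
| Treated +1.5, control −0.5 months, slopes −1 | 0.037 | 0.037 | 1.967 |
| As the row above, `t*` depending on C | 0.032 | 0.033 | 2.039 |
| Mean `t*` 12 in both arms, slopes −0.5 control, −0.2 treated | 1.988 | 1.988 | 1.987 |
| As row 3, propensity model wrong | −0.100 | 0.022 | 1.987 |
| As row 4, propensity model wrong | 0.071 | 0.037 | 1.980 |

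The formula in step 3 predicts 2 − 0.17 = 1.83, 2 − 0.2 = 1.80 and 2 − 1.5 − 0.5 = 0.00 for the first three rows, in line with the results. With a correct propensity model, single-replicate differences between the first two estimators had SD at most 0.018 and maximum 0.062. With a wrong propensity model and a correct outcome model, the two estimators separate, but the one as written still misses 2.00.

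**5. Size within the protocol's window.** Assume starts spread evenly over the year between reviews, reviews 12 months apart, and a decline of 0.25 points per month in both arms. Starts in months 0–3 use the next review (`t*` 9–12, mean 10.5). Starts in months 9–12 need the following review (`t*` 12–15, mean 13.5). Other starts have no review inside 9–15 months. If the later review exists for a share f, mean treated `t*` is `(10.5 + 13.5f)/(1 + f)`. With controls at 12:

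- f = 0: 10.5, bias 0.25 × 1.5 = 0.38. At a mean of 10.6, as simulated with some spread in timing, it is 0.25 × 1.4 = 0.35. A separate simulation of this case with true effect 0 gave +0.38 as written, +0.35 for plain weighting and 0.00 with observed `t*` in the residual.
- f = 0.5: 17.25/1.5 = 11.5, bias 0.25 × 0.5 = 0.13.
- f = 0.75: 20.625/1.75 = 11.8, bias about 0.05.
- f = 1: 12.0, bias 0.

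The window caps the offset at 3 months × slope per arm: 0.75 points at 0.25 per month, about 0.5 at 0.17 per month.

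**The case against.** The section never writes out the estimator for this analysis. It does not say in so many words that the residual uses month 12, and an analyst might use observed `t*` there unprompted. The text is condensed and carries slips: it calls the previous outcome model equation 3, which is the propensity score, and equation 5 has an index misprint. So one could ask only for clarification. That softens the point but does not remove it. The estimator is carried over unchanged, it has one place for a prediction, the instruction fixes that prediction at month 12, and nothing elsewhere moves the outcome or the weights.

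Three stronger readings are tempting, and the documents do not support them.

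- A reader might infer that visit timing is ignored altogether, or that the result is identical to an analysis without time. Re-anchoring time 0 at prescription, choosing the review nearest month 12 and the 9–15 month window all still act. The equivalence is a large-sample result that needs a correct propensity model. Individual scatter around month 12 does no harm; only departures of an arm's mean `t*` from 12 do.
- A reader might take the first review after prescription without a window, with mean `t*` near 6 and a bias near 0.25 × 6 = 1.5 points. The 9–15 month window rules this out.
- A reader might extend the problem to the study's main results. The main UK analyses and all US analyses do not use equation 6.

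It also stands that 0.35 is towards the unfavourable end. Recruitment in period 3 is 2016–2017, so people indexed in 2016 can still have a later review by 2018. Those indexed in 2017 would need a 2019 review.

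**Conclusion.** The point holds on the plain reading of the additional-analysis section with equation 5. As written, the estimator does not target FEV1% at month 12 unless mean `t*` is 12 in both arms, and it is not doubly robust for that estimand. At an assumed decline of 0.25 points per month, the bias is about 0.35 points if only the first review after prescription can serve, and about 0.15 or less if half or more of the treated can also use a later one. The slope, the spread of start dates and the share with a later review are all assumptions, because the protocol gives none of them. This should be fixed, but it is not critical: it concerns one additional analysis, in one registry and one of three periods.

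**What to change.** State the estimator for this analysis explicitly:

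`mean{ m(a, C_i, t* = 12) + I(A_i = a)/P(A_i = a | C_i) × [Y_i − m(a, C_i, t*_i)] }`

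Month 12 is set only in the leading term, and each person's observed `t*` goes into the residual. Derive the standard error for this form, including estimation of the time slope, for example by bootstrap. The estimator's derivative with respect to an arm's slope is 12 minus the weighted mean `t*`, which is not generally zero, so slope estimation contributes to the variance. Correct the equation 3 cross-reference and the index in equation 5 at the same time.

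The cost is about one sentence in the plan, one line of code for the estimate and the revised standard error, with no new data. There are two downsides. The time correction rests on the linear `t*` terms of equation 6, which a correct propensity model does not protect. The standard error may also be slightly larger, because the time slope is now actually used. Reporting the distribution of `t*` by arm would show how much correction is being made.

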##### Diagnostics

The distribution of weights will be assessed using summary statistics and plots. Methods such as trimming or truncating will be considered to deal with extreme weights. Standardised mean differences will be used to compare the balance in the distribution of confounders between treatment and control groups in the original and weighted samples.

### Secondary outcomes

The secondary outcomes are prescription of intravenous antibiotics, per cent predicted FVC (FVC%) and BMI z-score. Analysis of the continuous outcomes (FVC% and BMI z-score) can be implemented as described above. Prescription of intravenous antibiotics will be treated as a time-to-event outcome (time to first prescription of intravenous antibiotics at home or in hospital) where censoring occurs at 365 days, or prior in the event of death or organ transplant. HRs will be estimated using Cox regression for the outcome models.

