## Data sources

### UK CF registry

The UK CF Registry was established in 1995 and is a national database sponsored and managed by the CF Trust, with UK National Health Service research ethics approval. It records longitudinal data on approximately 99% of people with CF in the UK.^17 18^

Data are collected on time-invariant variables, such as sex at birth, cystic fibrosis transmembrane conductance regulator (*CFTR*) genotype, date of birth, diagnosis data and longitudinal variables that change over time. Longitudinal data are collected at approximately annual review clinic visits on over 250 variables covering several domains. These include clinical measurements taken on the day, and other variables covering the previous 12 months period such as: hospital admissions, treatments prescribed, culture and microbiology, health complications, nutrition, physiotherapy, smoking and outcomes (death and transplants). In 2016, the UK CF Registry started collecting treatment prescription start and stop dates.

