#### Covariates

In the target trial, individuals were randomly allocated to the treatment or placebo strategy. In the emulated trials, there is no randomisation. The data on treatment use within the UK and US CF Registries reflects treatment decisions made based on clinical indication and on clinician and patient preference. Being prescribed azithromycin is, therefore, assumed to be informed by a number of factors, many of which are also associated with the outcomes of interest. The association between prescription of azithromycin and FEV_1_% (and secondary outcomes) is, therefore, believed to be confounded by the following factors: age, number of days on intravenous antibiotics (intravenous days), non-intravenous hospital admissions, presence of *Pseudomonas aeruginosa*, *Staphylococcus aureus* or Nontuberculous Mycobacteria, pancreatic insufficiency, CF-related diabetes (CFRD), use of hypertonic saline or inhaled antibiotics and rate of decline in FEV_1_%, BMI z-score and FEV_1_%. These are depicted in a directed acyclic graph in figure 2.

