#### Notation

Let A denote an indicator variable for treatment strategy (A=0 indicates no prescription of azithromycin and A=1 indicates prescription of azithromycin). Let $Y_{t}\left(0\right)$ denote the potential outcome under treatment A=0 at time t,t∈{0,1} where t=1 is 12 months after t=0. Similarly, let $Y_{t}\left(1\right)$ denote the potential outcome under treatment A=1 at time t. Finally, C denotes the confounding factors listed in the section titled "Covariates" and in figure 2. In the following sections, we describe the causal estimand of interest, the main analysis plan with a focus on the primary outcome, and the key differences in the analyis plan for the secondary outcomes.

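### The FVC% analysis reuses a fixed confounder list that holds baseline FEV1% and BMI z-score but not baseline FVC%

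*Protocol article*

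**What the plan says.** All references are to the protocol article.

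- **Covariates** gives one confounder list and applies it beyond the primary outcome: "The association between prescription of azithromycin and FEV_1_% (and secondary outcomes) is, therefore, believed to be confounded by the following factors". The baseline clinical measures that close the list are "rate of decline in FEV_1_%, BMI z-score and FEV_1" (per cent predicted). FVC% is not among them.
- **Notation** defines C as that list together with figure 2. It also announces that "the key differences in the analyis plan for the secondary outcomes" will follow.
- **Secondary outcomes** states no difference for FVC%: "Analysis of the continuous outcomes (FVC% and BMI z-score) can be implemented as described above". The only departure described there is the time-to-event treatment of intravenous antibiotics.
- **Main analysis** explains the handling of the primary outcome: "In the emulated trials, we need to account for differences between treatment groups at baseline, including baseline FEV_1" (per cent predicted). It adds that adjusting for the baseline value can improve efficiency even when the groups are balanced.

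**The concern.** Equations 3 to 5 run with FVC% at time 1 as the outcome and C unchanged. FEV1% and BMI z-score each then have their own starting value in both models, and FVC% has only FEV1% as a stand-in.

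Two things are at stake. The first is precision: a measure's own earlier value is usually among its best predictors, and the outcome model would not use it. The second is confounding: if prescribing relates to FVC% beyond what FEV1% and the rest of C capture, the FVC% contrast absorbs part of that baseline difference.

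The plan's safeguards would not show either problem. The balance check in Diagnostics compares confounders, so a variable outside C is not examined. The E-value analysis is motivated by factors the registries do not capture, whereas FVC% is a registry measure.

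The comparison with the target trial is also touched. Table 2 lists changes in FVC as that trial's outcome, while the emulation takes the level at time 1. Without randomisation, estimates of change and of level agree only if baseline FVC% is balanced after adjustment.

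**Working it through.** **What the text fixes**

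| Continuous outcome | Own baseline value in C? |
|---|---|
| FEV1% (primary) | Yes, plus recent decline |
| BMI z-score | Yes |
| FVC% | No |

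**No figure to reproduce.** The article gives no SD, correlation or sample size for FVC%. What follows is an illustration, and every numerical input is an assumption.

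Let X = baseline FEV1%, Z = baseline FVC% and Y = FVC% at time 1, all standardised.

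- r(XZ): 0.7, 0.8, 0.9.
- r(ZY): 0.7, 0.8, 0.85.
- r(XY): either r(XZ) × r(ZY), meaning that FEV1% relates to later FVC% only through baseline FVC%, or that product plus 0.05.
- SD of FVC%: 15 points.
- Imbalance in Z remaining after adjustment: 0, 0.1 or 0.2 SD.

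Formulas:

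- Residual variance without Z: V1 = 1 − r(XY)²
- Coefficient of Z given X: bZ = [r(ZY) − r(XZ) r(XY)] / [1 − r(XZ)²]
- Coefficient of X given Z: bX = [r(XY) − r(XZ) r(ZY)] / [1 − r(XZ)²]
- Residual variance with Z: V2 = 1 − [bX r(XY) + bZ r(ZY)]
- Ratio of standard errors, without to with Z: √(V1/V2)
- Bias = bZ × imbalance in SD × 15

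Worst case for precision (0.7, 0.85, 0.595): V1 = 1 − 0.354 = 0.646; bZ = (0.85 − 0.4165)/0.51 = 0.85; bX = 0; V2 = 1 − 0.7225 = 0.2775; ratio = √(0.646/0.2775) = 1.53.

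Mildest case (0.9, 0.7, 0.68): V1 = 1 − 0.4624 = 0.538; bZ = (0.7 − 0.612)/0.19 = 0.46; bX = 0.05/0.19 = 0.26; V2 = 1 − (0.179 + 0.324) = 0.497; ratio = √(0.538/0.497) = 1.04.

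| r(XZ) | r(ZY) | r(XY) | SE ratio | bZ | Bias at 0 SD | at 0.1 SD | at 0.2 SD |
|---|---|---|---|---|---|---|---|
| 0.9 | 0.7 | 0.68 | 1.04 | 0.46 | 0 | 0.69 | 1.39 |
| 0.8 | 0.8 | 0.69 | 1.22 | 0.69 | 0 | 1.03 | 2.07 |
| 0.8 | 0.8 | 0.64 | 1.28 | 0.80 | 0 | 1.20 | 2.40 |
| 0.7 | 0.85 | 0.595 | 1.53 | 0.85 | 0 | 1.28 | 2.55 |

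Across all 18 combinations the SE ratio runs from 1.04 to 1.53. The bias is about 0.7 to 1.3 points at 0.1 SD of remaining imbalance and about 1.4 to 2.6 points at 0.2 SD.

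**Limits of the illustration.** It conditions on baseline FEV1% alone, whereas the planned models contain the rest of C. It also treats the outcome-model residual variance as driving the AIPTW standard error. That is only approximate, because adding Z to the propensity model changes the weights too.

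**The case against.** **The phrase may mean that each outcome's own baseline is substituted.** Notation says the main plan is described with the primary outcome in focus, so carrying the method over to FVC% could imply baseline FVC%. That is a sensible intention, but the text does not state it. C is explicitly defined as one list, and the list is said to cover the secondary outcomes. Two analysts could run different models. Nor can this simply be put down to a fuller plan, since Rationale and background says the article includes the statistical analysis plan.

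**A reader might infer that the FVC% contrast is confounded.** The documents do not show this. It needs FVC% to differ between groups after baseline FEV1%, its decline, BMI z-score, age, intravenous days, infections and the rest of C are controlled, and nothing in the article speaks to that. FEV1% may be a good proxy. The stated identifying condition is exchangeability given C. Equations 1 and 2 say only that the change and end-of-follow-up estimands coincide; they do not require baseline balance. Residual confounding is possible and no more. This objection stands.

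**A reader might also infer that sex, *CFTR* genotype and calendar year belong in C for every outcome.** The UK registry does hold "time-invariant variables, such as sex at birth" and genotype, but being collected does not make a variable a confounder: it must also influence prescribing given C. The article says C was informed by a directed acyclic graph, and figure 2 is not available here. Lung function is expressed as per cent predicted, and pancreatic insufficiency may carry part of the genotype information. The description of the US registry does not name genotype. Calendar year can vary only within a two-year recruitment window. A variable that predicts treatment but not outcome can inflate the weights. These additions are a preference, not a defect of the plan.

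**It is one secondary outcome, and samples are expected to be large.** True. That limits the consequence, but it does not explain the inconsistency.

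**Conclusion.** The point holds for FVC% only. As written, it is the one continuous outcome without its own baseline value in the propensity and outcome models, which departs from the plan's own reasoning for FEV1%. BMI z-score, named in the same sentence, is already covered, and the primary comparison is untouched.

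Some loss of precision is to be expected: every assumed scenario shows one, from about 4% to 53% in interval width. Bias is conditional: none if baseline FVC% is balanced given C, and roughly 0.7 to 2.6 FVC% points if 0.1 to 0.2 SD of imbalance remains. These sizes rest wholly on the assumed correlations, SD and imbalance. A narrower range would claim more than the documents allow.

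**What to change.** Add to Secondary outcomes that each continuous outcome's own baseline value enters both the propensity model and the outcome model. For the FVC% analysis, index-visit FVC% (from the same visit as baseline FEV1% in each registry) is then added to C. Include it in the standardised mean differences reported for that analysis.

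The baseline value should be obtainable: in the UK emulation, index and follow-up visits are both annual reviews, and FVC% is already to be taken from the follow-up visit. The cost is one sentence, one more model term, and some missing baseline FVC% values to handle under the missing-data plan. No change to C is needed for FEV1% or BMI z-score.

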### US CF registry

The US CF Registry began collecting data on people with CF in the USA in 1986 and is managed by the CF Foundation. It contains longitudinal information on approximately 80% of people with CF in the USA.^19^,^21^

Data are collected on demographic characteristics and on longitudinal variables that change over time. Data collection takes place at ‘encounter visits’ at CF care centres, with data also being abstracted annually. This study will use the encounter visit data which includes relevant information regarding hospitalisations, clinical measurements, medication usage, culture and microbiology, health complications. The encounter visits include routine clinical visits and visits in a hospital or the individual’s home. The non-routine hospital and home intravenous visits may be due to an individual experiencing worsening of their respiratory symptoms, and therefore, their lung function may be unstable at this time. These are referred to as ‘unstable’ visits, whereas routine clinical visits are referred to as ‘stable’ visits. The analyses in this study will use data from the stable visits only.

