Treatment strategies	The active intervention was azithromycin supplied as 250 mg tablets and the comparator was placebo pills.Individuals weighing less than 40 kg took one tablet 3 days per week, and individuals weighing more than 40 kg took two tablets 3 days per week.	The active intervention is prescription of oral azithromycin and the comparator is no prescription of oral azithromycin.Further details are provided in the section titled "Treatment strategies".	
Assignment procedures	Individuals were randomised to treatment strategy. Randomisation was stratified according to centre and *Pseudomonas aeruginosa* infection status. The patients and all study investigators remained blinded to the treatment assignment until study completion.	In the emulated trials, individuals are not randomly assigned to the treatment strategy. This is accounted for in the analysis.	
Follow-up period	12 months	As in the target trial	
Outcome	Primary outcome: mean change in FEV_1_% between month 0 and month 12.Secondary outcomes included: evaluation of the number of pulmonary exacerbations, the use of antibiotics, modifications of microbiological analysis of sputum or throat cultures, changes in FVC, nutritional status with measurement of body mass index (BMI) and quality of life.	Primary outcome: absolute FEV_1_% at the end of follow-up.Secondary outcomes include: prescription of intravenous antibiotics, FVC, BMI z-score.Further details are provided in the section titled "Outcomes".	
Causal contrasts of interest	Intention to treat	Per-protocol	
Analysis plan	For continuous outcomes, mean differences between treatment groups were estimated using mixed models; for binary outcomes, logistic regression was used; for count outcomes, Poisson regression was used.	A direct acyclic graph is used to inform which variables need to be controlled for (see sectiontitled "covariates").Confounding by measured variables will be accounted for using inverse-probability-of-treatment weighting.Further details are provided in the section titled "Data analysis".	

CFcystic fibrosisFEV_1_forced expiratory volume in 1 sFVCforced vital capacity

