#### Outcomes

Where possible, the emulated trials will replicate outcomes studied in the target trial; however, data are not available in the registries for all secondary outcomes. The primary outcome in the target trial, and both emulated trials, is absolute FEV_1_% at time 1. Secondary outcomes in the target trial include: number of pulmonary exacerbations, forced vital capacity (FVC), nutritional status with body mass index (BMI) z-score, the use of antibiotics, modifications of microbiological analysis of sputum or throat cultures and quality of life. Secondary outcomes in the emulated trials include:

Prescription of intravenous antibiotics at time 1 (as a proxy for pulmonary exacerbations).Percent predicted FVC at time 1.BMI z-score at time 1.

For the emulated trials, FEV_1_% will be calculated using the Global Lung Initiative (GLI) 2012 equations^25^ and BMI z-scores will be calculated using the WHO reference distribution.^26^

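### The intravenous-antibiotic outcome has two definitions and an effect measure that the stated estimator does not yield; in the UK annual-review analyses it also counts events before treatment

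*Protocol article*

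**What the plan says.** All references are to the protocol article.

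- **Outcomes** lists the endpoint as "Prescription of intravenous antibiotics at time 1 (as a proxy for pulmonary exacerbations".
- **Secondary outcomes** describes it instead as "time to first prescription of intravenous antibiotics at home or in hospital". The censoring rule given there is that "censoring occurs at 365 days, or prior in the event of death or organ transplant". On the effect measure, the same section says: "HRs will be estimated using Cox regression for the outcome models".
- **Main analysis** gives one AIPTW estimator, equation 5. It averages over individuals to estimate E[Y1(1)] and E[Y1(0)], and "the difference between these two expectations is an estimate of the average treatment effect in the population".
- **Definition of time 0 and the index visit** puts time 0 at the index visit.
- **UK CF Registry Data** (annual-review analysis) assigns people to the treated group if azithromycin is recorded at the follow-up visit, 9–15 months after time 0. The section on the additional UK analysis concedes that treatment may begin anywhere between time 0 and time 1. In period 3 only, the prescription-date analysis moves time 0 for treated people to their first prescription after the index visit.
- **US CF Registry Data** reads treatment at the index visit and censors controls who later start azithromycin. The article also says of the US data: "The analyses in this study will use data from the stable visits only".

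**The concern.** This endpoint is the emulations' stand-in for pulmonary exacerbations. Three things are unsettled.

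1. A status at a visit and a time to first event are different endpoints, needing different data and models.
2. A hazard ratio is not what equation 5 returns, and no step is given that turns a Cox outcome model into a marginal contrast or handles censoring. The article's reason for choosing AIPTW is double robustness. Whether that property carries over to the reported hazard ratio cannot be told.
3. In the UK annual-review analyses, exposure is defined by what happens after the event clock has started. A person who has an IV course in month 3 and starts azithromycin in month 6 contributes a treated-group event that azithromycin could not have prevented. Because the follow-up visit may fall as late as month 15 while events are counted to day 365, a treated person may even have started after the whole event window closed.

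The third matters most. The article names IV days among the factors informing azithromycin prescription, so starts that follow an IV course are plausible. Such starts push the hazard ratio against treatment.

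**Working it through.** The article gives no event rate, sample size or power figure for this outcome, so there is no stated figure to reproduce. The check sets the sections side by side and then sizes the timing problem under stated assumptions.

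**Definition.** In the UK, annual-review treatment records cover the past year, so time 1 could be shorthand for the preceding 12 months. In the US, time 1 is a single encounter visit and that reading is not available. The two sections need the same wording.

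**Effect measure.** Equation 5 takes an observed Y1 and a predicted mean of Y1. It has no term for censored follow-up and produces a mean difference. To show that a covariate-adjusted Cox hazard ratio differs from a marginal one even without confounding, treatment was randomised in simulation with baseline event rate 0.6 per year, one year of follow-up, conditional hazard ratio 0.60 and one standard-normal prognostic covariate (all assumed):

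| Covariate log hazard ratio | Conditional HR | Marginal HR |
|---|---|---|
| 0.5 | 0.60 | 0.62 |
| 1.0 | 0.60 | 0.67 |
| 1.5 | 0.60 | 0.72 |

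**Pre-treatment events, UK annual-review rule.** Assumed inputs:

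- Untreated 12-month IV risk of 20%, 40% or 60%, with hazard λ = −ln(1 − risk), that is 0.22, 0.51 or 0.92 per year.
- Azithromycin start hazard of 0.35 per year, so that 1 − exp(−0.35) = 0.30 start within the year.
- Start hazard multiplied by k = 1, 2 or 3 after a first IV course.
- Event hazard after starting of λ × true HR.
- No baseline confounding.

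Following the plan, A = 1 for a start at any time in the 12 months, the clock runs from the index visit, and a Cox model is fitted with censoring at one year. Ranges are over the three risks:

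| True HR | k | Treated first events before azithromycin | Estimated HR |
|---|---|---|---|
| 1.0 | 1 | 50–54% | 0.99–1.04 |
| 1.0 | 2–3 | 63–75% | 1.48–2.20 |
| 0.5 | 1 | 64–67% | 0.74–0.75 |
| 0.5 | 2–3 | 76–83% | 1.19–1.86 |

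Hand check of the third row: treated people spend on average 0.53 of the year on the drug and 0.47 off it, so the average hazard ratio is about 0.47 × 1 + 0.53 × 0.5 = 0.735, in line with 0.74–0.75.

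**The case against.** The strongest reply is that this is one secondary outcome, openly called a proxy, in a condensed article. The Outcomes section is a summary list and Secondary outcomes gives the operational definition. Late initiation is disclosed as a limitation and, in period 3, time 0 is realigned. Reversal of direction needs starts triggered by IV courses, for which no rate is given. Much of this stands and limits the point:

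- **Size.** With starts unrelated to events, a null effect is not biased. The result is also sensitive to the background start rate. With an IV rate of 0.5 per year and 5–30% starting after a course (assumed), a null effect appears as 1.64–3.93 at a background of 0.05 per year, 1.18–1.97 at 0.35 and 1.10–1.69 at 0.5. A reader might infer a fourfold distortion, but only low background rates produce one, and nothing in the article supports choosing them.
- **Cox versus Poisson.** For the target trial, Table 2 says "for count outcomes, Poisson regression was used" and lists no Cox model. A reader might infer that Cox is therefore wrong. A different model is not an error in itself, and direction and significance could still be compared. What is awkward is that the comparison criteria are written for ATE estimates and the target's confidence interval, against which a time-to-first-event hazard ratio cannot be set directly.
- **Conditional or weighted.** The article does not say which kind of hazard ratio is meant, so it cannot be called conditional or singly robust as a fact. It is unspecified.
- **US stable-visit rule.** A reader might infer that this rule deletes the outcome. The documents do not support that. Covariates says the registries hold IV treatment dates for home and hospital, the outcome includes both settings, and the rule is explained by unstable lung function. Only its scope needs a sentence.

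What does not fall away is the UK timing. Disclosure does not remove it, and the period 3 outcome model (equation 6) is written for FEV1% only.

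**Conclusion.** The point holds in limited form. The two definitions must be reconciled, and the reported measure does not match the stated estimator. In the UK annual-review analyses of all three periods, treated-group events can precede treatment. Under the assumed rates a true hazard ratio of 0.5 is diluted to about 0.75 when starts are unrelated to courses. When a course raises the start rate two- to threefold, it appears as about 1.2–1.9 and a null effect as about 1.5–2.2. The mechanism follows from the article's own definitions; the sizes do not.

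The timing problem does not apply to the US emulations, where treatment is read at the index visit. Nor does it put pre-treatment events into the treated group in the period 3 prescription-date analysis. It should not be read as a criticism of the primary FEV1% estimand. This should be fixed, at the level of one secondary proxy outcome.

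**What to change.** 1. **One definition.** Use the same endpoint in Outcomes and Secondary outcomes, built from IV course dates over the 365 days after time 0.
2. **A marginal contrast.** Report something AIPTW can deliver, such as the 12-month risk difference or ratio, or a marginal rate ratio if courses are counted. Build censoring for death, transplant and US controls who start azithromycin into the estimator; the last is missing from the censoring list under Secondary outcomes.
3. **UK timing.** Take the causal estimate from the period 3 prescription-date analysis, with IV history updated to each treated person's own time 0. Label the annual-review result, in every period, as descriptive because events can precede treatment. Say also how untreated time before a late start is handled, since that analysis realigns only the treated clock.
4. **US scope.** State that the stable-visit rule governs lung function and BMI, not IV course dates.

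Counting UK courses in the year after the follow-up review is not a good substitute. It would study people already on treatment, with eligibility and covariates 9–15 months old, and would run past the three-year windows.

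The cost is wording and code. The real loss is that UK periods 1 and 2 give no causal estimate for this outcome.
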